# STOP-RIO study: protocol for a randomised, controlled, open-label non-inferiority trial to test the safety of discontinuation of riociguat after balloon pulmonary angioplasty in chronic thromboembolic pulmonary hypertension

**DOI:** 10.1136/bmjopen-2026-120820

**Published:** 2026-08-07

**Keywords:** Cardiovascular Disease, Hemodynamics, Thromboembolism, Pulmonary Disease

## Abstract

**Introduction:**

Balloon pulmonary angioplasty (BPA) improves haemodynamics and outcomes in patients with inoperable chronic thromboembolic pulmonary hypertension (CTEPH). Riociguat is frequently initiated before BPA to reduce procedural risks. However, evidence supporting continuation after successful BPA is lacking and current guidelines provide no criteria for treatment discontinuation. Consequently, many patients remain on long-term riociguat despite uncertain benefit, potential adverse effects and high costs.

**Methods and analysis:**

STOP-RIO is a multicentre, open-label, randomised, non-inferiority (NI) trial conducted in the two Dutch CTEPH expert centres. Seventy-four adult CTEPH patients treated with riociguat monotherapy with a mean pulmonary artery pressure (mPAP) <30 mmHg post-BPA will be randomised (1:1) to stop or continue the medication. The primary endpoint is the between-group difference in baseline-adjusted mPAP at rest measured by right heart catheterisation at 16 weeks. NI will be tested for the primary endpoint and for the two secondary endpoints highest in hierarchy N-terminal pro-B-type natriuretic peptide and 6-min walk distance. Additional secondary endpoints include haemodynamic parameters, safety outcomes, patient-reported outcomes and healthcare use. The primary analysis will be performed in a per-protocol population with secondary intention-to-treat and exploratory analyses. A prospective health economic evaluation will be conducted from a societal perspective.

**Ethics and dissemination:**

The study is conducted in accordance with the Declaration of Helsinki and Good Clinical Practice and has received ethical approval. Written informed consent will be obtained from all participants. Results will be disseminated through peer-reviewed publication and shared with patient organisations and scientific congress.

**Trial registration number:**

EU Clinical Trials Register: 2024–5 19 225-38-00.

Strengths and limitations of this studyThis is a randomised, non-inferiority trial addressing a clinically relevant and unresolved question in chronic thromboembolic pulmonary hypertension (CTEPH) management.The study uses mean pulmonary artery pressure as a guideline-aligned and clinically interpretable primary endpoint.The multicentre design enhances generalisability within the Western CTEPH population.Most existing evidence on riociguat discontinuation originates from Japanese cohorts, where haemodynamic responses to balloon pulmonary angioplasty are generally more pronounced, underscoring the importance to evaluate a discontinuation strategy in a European context.The open-label design may influence subjective outcomes, although the primary haemodynamic endpoint is the objective.

## Introduction

 Chronic thromboembolic pulmonary hypertension (CTEPH) is a progressive disease resulting from persistent pulmonary artery obstruction and vascular remodelling, leading to elevated pulmonary artery pressure (PAP), right heart strain and increased mortality.^1
2^ In the European Union, prevalence is estimated at 30–50 per million.^1^ While pulmonary endarterectomy (PEA) is the preferred treatment, ~40% of patients are ineligible and undergo balloon pulmonary angioplasty (BPA), often preceded by pulmonary hypertension (PH) therapy to reduce PAP, lower bleeding risks of BPA and improve right ventricular function.^1–3^

Riociguat, a soluble guanylate cyclase stimulator, is the only approved drug for inoperable or persistent/recurrent CTEPH, demonstrating efficacy in the CHEST trials.^3–6^ Despite established benefits of riociguat in CTEPH, there is limited evidence supporting its continuation after BPA. Current guidelines allow for discontinuation after successful BPA but provide no definition of ‘success’ or criteria for patient selection.^1^ Consequently, many patients remain on riociguat indefinitely, despite side effects (eg, hypotension and dizziness), high societal costs (€33 000–51 000 per patient per year) and limited evidence to support long-term use.^7
8^

Preliminary data from Amsterdam UMC suggest that, following BPA, mean PAP (mPAP) is similar in patients treated with and without riociguat, implying that PAP reduction results primarily from desobstruction (figure 1). Another retrospective study also showed no significant difference in mPAP 1 year post-BPA between patients who discontinued PH medication and those who never received it.^9^ More recently, the multicentre, double-blind, randomised THERAPY-HYBRID-BPA trial evaluated the discontinuation of riociguat after BPA in 74 inoperable patients with CTEPH with normalised resting haemodynamics.^10^ Discontinuation did not result in a rebound increase in resting mPAP nor in differences in 6-min walk distance (6MWD) or B-type natriuretic peptide (BNP) levels compared with continuation. The primary endpoint, peak cardiac index during exercise, declined in the discontinuation group. However, translation to a Western population is limited by differences in patient characteristics and treatment strategies, while the clinical relevance of a higher peak exercise cardiac index remains uncertain, as riociguat may affect cardiac index independently from its effects on the pulmonary circulation, through direct cardiac effects or systemic vasodilation.^11–13^

**Figure 1 F1:**
[figure not shown]
mPAP before, during and after BPA in patients treated with riociguat (red, n=21) and in patients without PH-targeted therapy (blue, n=10). In the riociguat group, baseline measurement was obtained prior to treatment initiation. Mean (±SD) mPAP values in the riociguat group were 44.4±11.7 mmHg at baseline, 35.9±10.0 mmHg at first BPA, 29.3±6.7 mmHg at last BPA and 29.0±7.0 mmHg at follow-up. Corresponding values in the no-therapy group were 36.6±10.1 mmHg, 34.2±9.0 mmHg, 28.7±10.8 mmHg and 29.6±6.9 mmHg. BPA, balloon pulmonary angioplasty; mPAP, mean pulmonary artery pressure; PH, pulmonary hypertension.

Given the absence of prospective evidence in Western populations and the lack of standardised discontinuation criteria, this randomised non-inferiority (NI) trial aims to assess the safety and feasibility of stopping riociguat after BPA in patients with mPAP <30 mmHg (primary objective), including a prospective health economic evaluation of the societal and patient-related benefits of riociguat discontinuation (secondary objective).

## Methods

### Study design

This is a multicentre, open-label, randomised, controlled NI trial will include 74 CTEPH patients who reached an mPAP <30 mmHg post-BPA, comparing discontinuation versus continuation of riociguat post-BPA. The trial will be conducted at Amsterdam UMC and St. Antonius Hospital, the two Dutch national expert centres for CTEPH. To enhance generalisability, we aim to include additional European centres. Diagnosis of CTEPH, indication for BPA and initiation of riociguat therapy are a part of routine clinical care and fall outside the scope of the trial intervention. The estimated duration of the study is 2.5 years.

Ethical approval was obtained from the Medical Ethics Review Committee Amsterdam UMC (2025.0927) for the trial registered in the Clinical Trials Information System under registration number 2024–5 19 225-38-00.

### Study population

The study population consists of adult patients with CTEPH who are treated with riociguat monotherapy and have completed their final BPA session 6 months prior to screening. Patients are recruited from routine follow-up visits at the participating centres.

Eligible patients must have demonstrated an mPAP <30 mmHg on right heart catheterisation (RHC) performed within 3 months prior to inclusion. If no recent RHC is available, it will be performed after informed consent. Patients with an mPAP ≥30 mmHg are excluded.

Inclusion criteria include: age ≥18 years; diagnosis of CTEPH according to prevailing European guidelines; treatment with riociguat monotherapy initiated prior to or within 2 weeks after the first BPA session; availability of a documented post-BPA follow-up RHC performed within the last 3 months or an anticipated post-BPA follow-up RHC with an mPAP <30 mmHg as determined by the treating physician’s judgement; ability to comply with study procedures; and provision of written informed consent.

Exclusion criteria include: WHO functional class IV; cardiac index <2.2 L/min/m²; prior PEA; post-BPA follow-up RHC within 3 months indicating an mPAP ≥30 mmHg; participation in another interventional drug trial; severe comorbidities limiting life expectancy to less than 1 year; or any condition that, in the investigator’s judgement, precludes safe participation.

### Randomisation and allocation

After confirmation of eligibility and completion of baseline assessments, participants are randomised in a 1:1 ratio to either discontinuation or continuation of riociguat. Randomisation is performed in CastorEDC (Ciwit B.V., Amsterdam, The Netherlands) using block randomisation with variable block sizes. Stratification is applied by riociguat dose at inclusion (daily dose of <6 mg vs ≥6 mg) and time since last BPA, distinguishing incident patients (scheduled for RHC as part of standard clinical follow-up) from prevalent patients (those in long-term follow-up, screened by transthoracic echocardiography (TTE); last RHC performed more than 3 months ago). Due to the nature of the intervention, the trial is conducted as an open-label study. Blinding was considered impractical given the recognisable side effects of riociguat and the objective nature of the majority of primary and key secondary outcomes. However, all physicians performing outcome measurements will be blinded to treatment allocation.

### Interventions

Participants allocated to the control group continue riociguat at the pre-inclusion dose, administered three times a day in accordance with current clinical guidelines.^5
6^ Dose adjustments for hypotension or adverse effects are permitted at the discretion of the treating physician. Participants allocated to the intervention group discontinue riociguat following a structured tapering schedule over 6 days. Treatment is reduced from 2.5 mg three times a day to 2.0 mg three times a day for 2 days, followed by 1.0 mg three times a day for 2 days, after which the medication is discontinued. Participants receiving a lower dose at baseline will enter the tapering schedule at the corresponding step and may skip preceding dose-reduction steps. In case of clinical worsening during follow-up, riociguat is re-initiated at 1.0 mg three times a day for 2 weeks, followed by up-titration to the pre-inclusion dose as tolerated, in accordance with clinical guidelines.^5
6^

### Follow-up and safety monitoring

The study protocol is outlined in figure 2. Baseline assessments include RHC, cardiopulmonary exercise testing, 6MWD with Borg dyspnoea score, TTE, laboratory testing (including N-terminal pro-BNP (NT-proBNP)), and quality of life questionnaires. These assessments will be repeated at 16 weeks (end of study). Monthly follow-up is performed by outpatient visits or telephone contact to assess symptoms, medication adherence and adverse events (AEs). AEs are collected using open-ended and structured queries, including predefined symptoms such as dizziness and diarrhoea. Blood pressure is measured at each contact; hypotension (≤90/60 mmHg) is graded (grade 1–5) according to Common Terminology Criteria for Adverse Events (CTCAE) v5.0.^14^ Participants have 24/7 access to their PH care team.

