**Figure 2 F2:**
[figure not shown]
Outline of study protocol. At the end of study follow-up, participants will also complete a survey assessing satisfaction with the discontinuation strategy. 6MWD, 6-min walking distance; CPET, cardiopulmonary exercise testing; FC, functional class; QoL, quality of life; RHC, right heart catheterisation; TTE, transthoracic echocardiogram.

A predefined safety evaluation is performed at week 8 (±3 weeks). Clinical worsening is defined as the simultaneous occurrence of all three of the following criteria: (1) >15% decrease in 6MWD, (2) progression to WHO functional class III/IV, and (3) increase in NT-proBNP of ≥30% to a level of ≥300 pg/mL. This definition is adapted from prior pulmonary arterial hypertension (PAH) and CTEPH trials and aligns with criteria used in the STELLAR trial.^3
15–18^ If clinical worsening is confirmed, TTE is performed and riociguat is reinitiated in the discontinuation group. Unscheduled evaluations may be performed at the investigator’s discretion in case of suspected clinical deterioration.

At study completion, participants complete a survey assessing satisfaction with the discontinuation strategy. Riociguat may be reintroduced after the end-of-study RHC at the discretion of the treating physician and patient.

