### Objectives and endpoints

The primary endpoint is the between-group difference in mPAP at rest, measured by RHC at 16 weeks. Secondary endpoints for the primary study objective are outlined in table 1.

**Table 1 T1:** Secondary outcomes for the primary study objective

Objectives	Secondary endpoints
To investigate if discontinuation of riociguat is non-inferior to its continuation in CTEPH patients with mPAP <30 mmHg post-BPA	Efficacy endpoints: Between-group differences at 16 weeks for the following parameters in hierarchical order: NT-proBNP (assessed for non-inferiority) 6MWD (assessed for non-inferiority) PVR Cardiac index Between-group differences at 16 weeks in exercise capacity in post hoc analysis: CPET variables: oxygen uptake, workload, heart rate, respiratory exchange ratio, ventilation, oxygen saturation, oxygen pulse, equivalent carbon dioxide Change in modified Borg dyspnoea scale Safety endpoints: Between-group differences at 16 weeks in the following parameters: Number of adverse events and severe adverse events Proportion of participants with mPAP ≥38 mmHg at RHC Proportion of participants meeting the clinical worsening criteria at week 8 Feasibility of the strategy: Is TTE sufficient to replace RHC at the end of study follow-up? The correlation between TTE and RHC parameters Right ventricular systolic pressure Tricuspid annular plane systolic excursion Proportion of participants missed by TTE with mPAP ≥38 mmHg at 16 weeks RHC Is the discontinuation strategy feasible for implementation in clinical practice? Proportion of participants missed by the clinical worsening criteria with mPAP ≥38 mmHg at 16 weeks Participants' satisfaction with the protocol

BPA, balloon angioplasty; CPET, cardiopulmonary exercise testing; CTEPH, chronic thrombo-embolic pulmonary hypertension; mPAP, mean pulmonary artery pressure; 6MWD, 6-min walking distance; NT-proBNP, N-terminal pro-B-type natriuretic peptide; PVR, pulmonary vascular resistance; RHC, right heart catheterisation; TTE, transthoracic echocardiography; WHO, world health organisation.

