### Health economic evaluation

A prospective economic evaluation will be conducted after completion of the trial. Costs related to medication use, healthcare consumption (including outpatient visits, hospital admissions and emergency department visits) and patient travel will be collected prospectively. Health-related quality of life will be assessed using the EuroQol five-dimensional five-level questionnaire (EQ-5D-5L) and Living with Pulmonary Hypertension Questionnaire (LPHQ). These outcomes will be incorporated into a formal health-economic evaluation to estimate cost-effectiveness in terms of quality-adjusted life years. Secondary endpoints for the secondary study objectives are outlined in table 2.

**Table 2 T2:** Secondary endpoints for the secondary objectives

Secondary objectives	Endpoints for secondary objectives
To assess the societal impact benefits associated with riociguat discontinuation in CTEPH patients with mPAP <30 mmHg post-BPA	Economic outcomes Between-group difference in costs related to PH medication Between-group difference in healthcare consumption Frequency of visits to expert centres versus local hospitals Travel distance for medical care Number of emergency department visits Patient-related outcomes Between-group difference at 16 weeks in the following parameters: WHO functional class Quality of life questionnaire scores LPHQ EQ-5D-5L Number of predefined graded adverse events: Mean gradation of hypotension Mean gradation of dizziness Mean gradation of diarrhoea

BPA, balloon angioplasty; CTEPH, chronic thrombo-embolic pulmonary hypertension; EQ-5D-5L, EuroQol five-dimensional five-level questionnaire ; LPHQ, Living with PH questionnaire; mPAP, mean pulmonary artery pressure; PH, pulmonary hypertension.

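### The adverse events named for prompting and grading are all riociguat-type, so the pooled adverse-event count in Table 1 is hard to interpret and could favour discontinuation

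*Protocol article*

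**What the plan says.** Three parts of the protocol article bear on this.

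- **Collection** (Follow-up and safety monitoring). Contacts are monthly and the same for both arms: "Monthly follow-up is performed by outpatient visits or telephone contact to assess symptoms, medication adherence and adverse events (AEs". On method: "AEs are collected using open-ended and structured queries, including predefined symptoms such as dizziness and diarrhoea". One further event is measured: "Blood pressure is measured at each contact; hypotension (≤90/60 mmHg) is graded (grade 1–5", using CTCAE v5.0.
- **Graded events as endpoints** (Health economic evaluation, Table 2). The entry reads "Number of predefined graded adverse events: Mean gradation of hypotension Mean gradation of dizziness Mean gradation of diarrhoea". It serves this objective: "To assess the societal impact benefits associated with riociguat discontinuation in CTEPH patients with mPAP <30 mmHg post-BPA".
- **The safety comparison** (Objectives and endpoints, Table 1). Under the non-inferiority objective, the first safety endpoint compared between groups at 16 weeks is "Number of adverse events and severe adverse events". It is not split by how an event came to be recorded.

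The Introduction describes patients staying on riociguat "despite side effects (eg, hypotension and dizziness". The trial is open-label. The blinding described under Randomisation and allocation covers physicians who perform outcome measurements, not the patients who report symptoms.

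**The concern.** Both arms have the same contacts and the same questions, but that does not by itself make the count even-handed. A symptom that is asked about by name is usually recorded more completely than one the patient must raise. All the events named for asking, measuring or grading are of a kind expected more often on riociguat. Those expected more often after stopping, such as breathlessness, oedema, fatigue or syncope, are not named. Completeness of recording could therefore differ by type of event, and type of event goes with the arm.

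At stake is a safety result that will be reported in its own right under the non-inferiority objective. A lower total after stopping would be read as support for stopping, although part of it could come from the questions asked. The graded-event endpoint in Table 2 shares the limit, because it can register only the side of the balance on which stopping is expected to do better.

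**Working it through.** The article gives no adverse-event rate, capture rate or power for this endpoint, so there is no figure to reproduce. The check has two parts.

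**1. The named events side by side**

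| Event | How it is actively sought | Link to riociguat in the article |
|---|---|---|
| Hypotension | Measured at each contact, graded | Called a side effect in the Introduction |
| Dizziness | Structured query; graded in Table 2 | Called a side effect in the Introduction |
| Diarrhoea | Structured query; graded in Table 2 | Implied only, by its place in Table 2 |
| Any symptom of deterioration | None named as a prompted or graded adverse event | – |

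The wording on structured queries gives examples, so the query list is open. The Table 2 list carries no such qualifier. The one-sided grading is therefore stated, while one-sided prompting is only possible.

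**2. What unequal capture would do to the count**

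Input from the documents: 74 participants allocated 1:1, so 37 per arm. Everything else is assumed:
- equal true harm, with one event per patient in each arm;
- *s* = share of an arm's events that are typical of that arm (drug-type on continuation, withdrawal-type on stopping);
- *p* = capture of prompted events = 0.90;
- *u* = capture of unprompted events, varied;
- no withdrawal-type symptom is prompted.

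Recorded events are 37 × [*s·p* + (1 − *s*)·*u*] on continuation and 37 × [*s·u* + (1 − *s*)·*p*] on stopping.

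With *s* = 1, continuation records 37 × 0.90 = 33.3. Stopping records 37 × 0.80 = 29.6, 37 × 0.70 = 25.9 or 37 × 0.50 = 18.5.

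Ratio of recorded events, stop to continue (truth 1.00):

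| *s* | *u* = 0.90 | 0.80 | 0.70 | 0.50 |
|---|---|---|---|---|
| 1.00 | 1.00 | 0.89 | 0.78 | 0.56 |
| 0.75 | 1.00 | 0.94 | 0.88 | 0.75 |
| 0.50 | 1.00 | 1.00 | 1.00 | 1.00 |

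Example for *s* = 0.75 and *u* = 0.70: (0.75 × 0.70 + 0.25 × 0.90) / (0.75 × 0.90 + 0.25 × 0.70) = 0.75 / 0.85 = 0.88.

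The 37 cancels from the ratio, so the table only restates the assumed capture rates and mix of events. It shows how the mechanism works and does not estimate its size.

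**Direction.** Suppose that awareness of having stopped multiplies recorded unprompted complaints in that arm by *k*. With *s* = 1, the ratio returns to 1.00 when *k* = 0.90 / *u*, which is 1.13, 1.29 or 1.80 for *u* = 0.80, 0.70 or 0.50. A larger *k* turns the count against discontinuation. The documents give no basis for choosing *k*.

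**The case against.** The strongest reply is that the sentence on structured queries gives examples. The full list may be in the complete protocol or the eCRF, which an article need not reproduce, and monthly contacts also assess symptoms in general. Table 2 lists endpoints for the objective on benefits and is not an inventory of what is asked. This stands as far as prompting goes. It does not remove the one-sided graded list, which Table 2 fixes, or the pooled count, which Table 1 fixes.

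Harm from stopping is also sought actively in both arms: "A predefined safety evaluation is performed at week 8 (±3 weeks", with 6-minute walk distance, WHO functional class and NT-proBNP. Clinical worsening and mPAP ≥38 mmHg are separate safety endpoints. Borg score, functional class, quality of life and emergency visits are collected too. This stands, and it protects the overall safety assessment. It does not correct the count: clinical worsening needs all three criteria at once, the mPAP threshold is haemodynamic, and nothing says that Borg or functional class findings become adverse events.

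The direction is also open to challenge. Patients who know that they have stopped may volunteer more complaints, continuing patients remain on a drug they already take, and dizziness need not arise only on the drug. This stands too.

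A reader might infer that the count is tilted towards discontinuation, or that harms of stopping rest on volunteered reports alone. The documents support neither: the query list is open, deterioration is measured by other means, and the net direction is unknown.

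**Conclusion.** The point holds as a conditional risk. Every event the article names for prompting or grading is riociguat-type, and a pooled count is then compared between open-label arms as a safety endpoint. If the structured list contains no deterioration symptoms, the pooled count and the graded-event endpoint could favour discontinuation. Neither the size nor the net direction can be derived. The ratios from 1.00 down to 0.56 rest on assumed capture rates and equal true harm, and vanish if capture is equal or each arm's events are an even mix of types.

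The reach is limited. The count has no non-inferiority margin, and non-inferiority is tested only for mPAP, NT-proBNP and 6-minute walk distance. The primary endpoint, clinical worsening, mPAP ≥38 mmHg, Borg score and WHO functional class are not affected. This is a worthwhile, inexpensive improvement and not a flaw in the main conclusion.

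**What to change.** 1. In the Table 1 comparison, report solicited events (hypotension, dizziness, diarrhoea and any others on the structured list) separately from unsolicited events, and do not rest the between-group safety statement on their sum. This changes analysis wording only.
2. Put a short list of deterioration symptoms (for example breathlessness, oedema, fatigue, syncope) in the structured query at the existing contacts in both arms. Grade them on the same CTCAE v5.0 scale and list them with the graded events in Table 2. If the full protocol already asks about them, one sentence saying so settles the prompting, and only the grading and listing remain.

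The second change costs a few questions per contact and a small eCRF change, and somewhat more mild events will be recorded in both arms. It should be made early, because symptoms not asked about during follow-up cannot be reliably recovered afterwards.
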